## (2) Malfunctions and adverse events (biotube)

- Major formation (insufficient length, strength, etc.):

If the length of the fabricated biotube is insufficient for bypass surgery alone due to poor formation, revascularization may be attempted by joining together multiple pieces of the biotube, or by anastomosis with an artificial blood vessel or autologous vein, etc. Also, if no usable pieces are formed at all, bypass surgery itself may not be possible.

- Deformation, breakage, rupture, damage, etc. during or after transplantation
- Poor revascularization due to thrombus formation, stenosis, or blockage

## (3) Other risks

If a sufficient implantation period cannot be secured or if the clinical trial needs to be terminated due to some reason, such as rapid progression of the primary disease, it may not be possible to perform bypass surgery even if BTM1 is implanted.

### 1.5.2 Anticipated benefits of using this test device

By using the biotube made with BTM1 for bypass surgery, it may be possible to treat patients who are difficult to treat with existing lower limb revascularization procedures. The possible benefits of performing bypass surgery using the biotube are shown below.

#### (1) Benefits of being able to revascularize using the biotube

Avoidance of major amputation, wound healing of ulcers, relief and elimination of pain, recovery of walking, improvement of activities of daily living, prevention of

decline in cognitive function, improvement of life prognosis (reduction in mortality rate), avoidance of contralateral limb amputation, reduction in medical costs

(2) Benefits of biotubes being autologous tissue

- It is less likely to cause infection, and even if an infection does occur, it is easier to manage than artificial objects.
- Even if it becomes blocked after implantation, it is naturally absorbed and does not need to be removed.

2. Clinical trial objectives

The purpose of this clinical trial is to evaluate the safety and effectiveness of bypass surgery to the leg artery below the knee or foot artery using a biotube created subcutaneously using the test device "BTM1" in patients with severe lower limb ischemia who do not have an optimal saphenous vein.

3. Clinical trial design

3.1 Types and designs of clinical trials

3.1.1 Types of clinical trials

Exploratory investigator-initiated clinical trials

3.1.2 Clinical trial design

Open-label, uncontrolled, multicenter clinical trials

[Rationale for setting]

This clinical trial was conducted as an open-label, uncontrolled study because there was no comparable medical device for patients with critical limb ischemia who do not have an optimal saphenous vein, and the purpose of the study was to exploratory investigate the efficacy and safety of using a biotube created subcutaneously using BTM1 in place of an autologous vein in bypass surgery to the leg artery or foot artery.

3.2 Evaluation items

(1) Efficacy evaluation items

1) Primary evaluation items

Ability of forming biotubes using the test device

2) Secondary evaluation item

- ① Procedural success of implantation and removal of the test device
- ② Procedural success of bypass surgery, including distal anastomosis, using a biotube formed by the test device
- ③ Patency of the biotube at 12 weeks after implantation
- ④ Improvement of symptoms (improvement of ischemic pain, improvement of wounds)
- ⑤ Avoidance of major amputation
- ⑥ Rate of additional treatment during implantation of the study device and after implantation of the biotube
- ⑦ QOL during implantation of the test device and after implantation of the biotube
- ⑧ Bypass graft diameter after bypass surgery

[Rationale for setting]

First, it is necessary to confirm that the biotube formed using the test device can be used in bypass surgery and function as a substitute blood vessel. Next, it is necessary to examine whether the treatment is effective and whether symptoms can be improved to avoid amputation. Since symptoms usually improve in 12 weeks with bypass surgery using veins, it is necessary to observe the patient for up to 12 weeks.

## (2) Safety evaluation items

- ① The occurrence of inflammation, tumor formation, or death that cannot be ruled out as being related to the test device during the period of subcutaneous implantation of the test device
- ② Biocompatibility of the implanted biotube (inflammation, rejection, tumor formation, etc.)
- ③ Burst of implanted biotubes
- ④ Deaths related to implanted biotubes cannot be ruled out
- ⑤ Deaths within 12 weeks after implantation of biotubes
- ⑥ Other adverse events and malfunctions

[Rationale for setting]

Since the medical device is implanted in the body, it is necessary to carefully check whether it has any adverse effects on the body. In addition, the formed biotube is made of the patient's own tissue, but since the tissue formed subcutaneously will be used as blood vessels in another part of the body, it is

necessary to confirm that it can be safely implanted without any malfunctions and functions as a blood vessel.

### 3.3 Subject participation period in the clinical trial

The participation period for each subject in the clinical trial will be from the date of consent to the end of the post-observation period (12 weeks after biotube implantation), excluding follow-up periods associated with adverse events.

### 3.4 Restrictions on case registration

Considering that this is the first clinical trial using BTM1 in humans, and to ensure the safety of subjects, the following measures will be taken to limit case enrollment.

- ① One month after transplantation, a "case enrollment limit" will be set, at which point the Efficacy and Safety Evaluation Committee will decide whether to continue the clinical trial.
- ② The restriction on case enrollment cannot be lifted at any of the medical institutions participating in the trial until one successful case has been achieved.
- ③ Case registration at other participating medical institutions will not be possible until one successful case has been achieved by the third case at the first participating medical institution.
- ④ The clinical trial will be terminated if three consecutive cases are unsuccessful at each participating medical institution, or across all participating medical institutions.
- ⑤ An Efficacy and Safety Evaluation Committee will be held for all cases one month after transplantation.
- ⑥ If any problems arise, an Efficacy and Safety Evaluation Committee will be held each time.

### 3.5 Planned period of clinical trial

August 2022 to May 2026 (Registration period: August 2022 to November 2025)

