### 6.3 Subject Enrollment

- (1) The investigator or co-investigator shall verify the eligibility of subjects who have given consent as described in "6.1 Obtaining Consent" as described in "6.2 Eligibility Verification".
- (2) The investigator or subinvestigator shall register subjects who have been confirmed as eligible for this clinical trial in accordance with a procedure to be determined separately. After confirming that registration has been completed, the investigator or subinvestigator shall implant the investigational device.

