- 13) The biotube is removed from the core and washed with physiological saline.
- 14) A straightening rod is inserted into the lumen of the biotube and it is immersed in alcohol (70%) in an immersion dish for 30 minutes.
- 15) The biotube is washed again with saline, and visually inspected to ensure that there are no tears, defects, or significant deviations in wall thickness
- 16) Store in heparinized saline until use for transplantation.
- 17) As with bypass surgery using an autologous vein graft, load saline into the inside of the biotube with a syringe to confirm that there are no leaks,

and use a pressure monitor to check for pressure resistance (presence or absence of swelling or rupture under a pressure load of 200 mmHg). Also, use a tensile tester to measure the maximum strength and confirm that it meets the standard strength (5 N).

The biotube prepared using steps 1) to 17) above is transplanted into the subject's lower limb as a substitute blood vessel, in the same way as an autologous vein graft. If the investigational device cannot be removed and the biotube implanted on the same day due to the subject's general condition or other reasons, the prepared biotube may be temporarily stored. When temporarily storing, the biotube should be immersed in 10% alcohol while maintaining a sterile state, sealed, and stored at room temperature (if the prepared biotube is in fragments, it should be stored as is). In this case, the temporary storage period should be a maximum of 4 weeks, and the biotube implantation should be performed within 4 weeks of the investigational device removal. In addition, the investigator should make appropriate preparations before the start of the clinical trial, such as securing a storage location and creating storage procedures, to prevent loss or mix-up during temporary storage.

[Rationale for setting]

The results of non-clinical trials have confirmed that the shape and strength of the BioTube did not change significantly for six months at room temperature. From the above, it has been confirmed that temporary storage is possible, but in order to prevent the condition from worsening, it is preferable to transplant the BioTube as soon as possible, and at the latest within four weeks after removal of the test device. Therefore, the temporary storage period was set at a maximum of four weeks (at room temperature).

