#### 6.4.4 Implantation period of the test device and follow-up period

Implantation period of the test device: 4 to 24 weeks (in principle, 8 weeks or more)

Post-observation period: up to 12 weeks after implantation of the biotube

In addition, this period includes the pre-observation period from consent acquisition to registration (up to 8 days) and the follow-up period for adverse events (if adverse events that require follow-up occur).

[Rationale for setting]

The longer the implantation period, the more the tissue formation of the biotube progresses, but to avoid excessive worsening of the symptoms of lower limb ischemia, it is desirable to perform bypass surgery as soon as possible. Therefore, although it depends on the symptoms, the implantation period was set to about 2 months (8 weeks) in principle to ensure the formation of the biotube. In addition, since it was confirmed in non-clinical studies that the biotube could be formed after one month of implantation, it was considered acceptable to perform removal and bypass surgery even if the implantation period was between four and eight weeks if significant progression of ischemia was observed after implantation, and therefore the shortest implantation period was set at four weeks.

In addition, since symptoms usually improve around three months after implantation when bypass surgery is performed using an autologous vein, and since the results of non-clinical studies suggest that the implanted biotube is generally replaced by autologous tissue around three months after implantation, the observation period after implantation of the biotube was set at 12 weeks.

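### The planned trial period leaves 26 to 30 weeks after a November 2025 registration, but the protocol permits up to 40 weeks from device implantation to the 12-week visit

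*Protocol*

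**What the plan says.** Protocol section 3.5, and the duration row of the overview, state: "August 2022 to May 2026 (Registration period: August 2022 to November 2025". Only months are given.

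The length of a subject's course is set elsewhere:

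- Section 6.3, start of the device period: "After confirming that registration has been completed, the investigator or subinvestigator shall implant the investigational device". It sets no maximum interval between the two steps.
- Section 6.4.4, device period: "Implantation period of the test device: 4 to 24 weeks (in principle, 8 weeks or more". The rationale adds that "the implantation period was set to about 2 months (8 weeks) in principle".
- Section 6.4.2 (1), when removal and transplantation are not done on the same day: "the temporary storage period should be a maximum of 4 weeks".
- Section 6.4.4, follow-up: "Post-observation period: up to 12 weeks after implantation of the biotube". Section 3.3 has participation run to the "end of the post-observation period (12 weeks after biotube implantation".
- Section 4.4 (7): a subject who does not need bypass at 24 weeks has the devices removed and is discontinued, with formation ability still evaluated.

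None of these sections shortens the course, or extends the trial, for subjects registered late.

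**The concern.** The gap between the close of registration and the end of the trial should cover the longest course that the protocol permits. Here it does not. A subject registered near the close, with a long but permitted device period, would have Visit 13 after the stated end.

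Visit 13 supplies the 12-week patency result, the last symptom and WIfI assessments, the post-transplant questionnaire, and the end of observation for major amputation and for deaths within 12 weeks. With 12 subjects, one missing result is 8% of the trial. Any such gap would also be selective, because it would fall on long device times. Section 6.4.4 says tissue formation advances with time in place, so device time may be related to the outcome.

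**Working it through.** The protocol states no derived duration, so there is no figure of its own to reproduce. The check is calendar arithmetic.

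**Inputs**
- Registration closes in November 2025, taken as 1 or 30 November; the trial ends in May 2026, taken as 31 May (section 3.5).
- Registration to implantation: taken as 0 weeks, which favours the protocol (section 6.3 gives no limit).
- Device 4 to 24 weeks, usually about 8; follow-up 12 weeks (section 6.4.4). Storage 0 to 4 weeks (section 6.4.2 (1)).
- The "pre-observation period from consent acquisition to registration (up to 8 days") comes before registration and is not counted.

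**Window = trial end − registration date**
- From 30 November 2025 to 31 May 2026: 182 days / 7 = 26.0 weeks.
- From 1 November 2025 to 31 May 2026: 211 days / 7 = 30.1 weeks.

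**Course = device + storage + 12 weeks, for a subject implanted on 30 November 2025**

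| Device + storage + follow-up | Weeks | Visit 13 falls on | By 31 May 2026? |
|---|---|---|---|
| 4 + 0 + 12 | 16 | 22 March 2026 | yes |
| 8 + 0 + 12 | 20 | 19 April 2026 | yes |
| 8 + 4 + 12 | 24 | 17 May 2026 | yes |
| 24 + 0 + 12 | 36 | 9 August 2026 | no, 10 weeks late |
| 24 + 4 + 12 | 40 | 6 September 2026 | no, 14 weeks late |

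**Largest device time plus storage that still fits = window − 12**
- Implanted 30 November: 26.0 − 12 = 14.0 weeks.
- Implanted 1 November: 30.1 − 12 = 18.1 weeks.

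**Bypass surgery itself.** Device plus storage can reach 24 + 4 = 28 weeks. For a 30 November registrant that exceeds 26.0, and surgery would fall on 14 June 2026. Removal at 24 weeks falls on 17 May 2026, inside the period.

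**Sensitivity to the end date.** With an end of 1 May 2026 the window is 21.7 to 25.9 weeks. For a 30 November registrant the 20-week course still fits, but the 24-week course does not.

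**Subjects exposed.** For a 40-week course to end by 31 May 2026, implantation must take place by 24 August 2025. From then to 30 November is 98 days (14 weeks). The registration period, 1 August 2022 to 30 November 2025, is 1,218 days (174 weeks). Under uniform accrual (an assumption), 12 × 98 / 1,218 = 0.97 subjects, or 8%.

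**Subjects affected.** An exposed subject is affected only if device time plus storage exceeds the remaining margin. As an illustration, suppose that total is spread evenly over 4 to 28 weeks, a width of 24. A subject registered x weeks before 30 November is then affected with probability (14 − x) / 24. Summed over x from 0 to 14, the expected number is (12 / 174) × (14² / 2) / 24 = 0.28. If no subject exceeds 14 weeks, it is 0.

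**The case against.** A reader might infer that late registrants in general cannot reach the 12-week endpoints. The protocol does not support that: the minimum course, the usual 8-week course, and the 8-week course with full storage all finish by 31 May 2026 even from a 30 November registration.

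The 40-week course also combines two exceptional circumstances. Section 6.4.4 wants bypass done early, and section 6.4.2 (1) allows storage only when same-day transplantation is not possible. Under section 4.4 (7), a subject who does not need bypass at 24 weeks leaves the trial and has no 12-week post-transplant result to lose; for a 30 November registrant this happens on 17 May 2026.

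Nor does the protocol say that data will be lost. Section 3.5 describes a planned period. Section 3.3 ends participation at 12 weeks after transplantation with no calendar limit, the discontinuation criteria contain no date, section 9 fixes no date for data fixation, and section 14.2 provides for revision. The likely response to one long late course is an extension. That the calendar would push sites towards earlier removal is likewise conjecture.

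All of this stands, and it narrows the point. It does not remove it: a subject who still needs bypass late in the 24-week period may proceed, and the stated dates do not accommodate that subject.

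**Conclusion.** The point holds in limited form. The planned period does not contain every course that the protocol permits: 26 to 30 weeks are available after a November 2025 registration, against a maximum of 40 (36 without storage). It fails for November registrants who proceed to bypass with device time plus storage above about 14 to 18 weeks.

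The exposure is mainly of the 12-week secondary and safety items. The primary item is touched only at the extreme. Formation is assessed at removal, which stays inside the period, but section 8.1 counts the item as achieved when bypass can be done with biotube alone. For a 30 November registrant that surgery falls outside only beyond 26 weeks.

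The figure of about 1 in 12 is the number exposed under uniform accrual, not the number lost. The number affected is smaller and cannot be fixed from the protocol, which gives neither device times nor an accrual forecast. Accrual weighted towards the end, which the enrolment limits in section 3.4 make plausible, would raise both numbers. The results rest on a 31 May end and no gap before implantation; an earlier end or any gap narrows the margin. Because the usual course fits and the remedy is a date, the severity is minor to moderate.

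**What to change.** Reconcile the planned period in section 3.5 and the overview with sections 6.4.2 and 6.4.4, in one of two ways:

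- move the trial end to about September 2026, which covers the 40-week course from 30 November 2025 (6 September 2026) if implantation follows registration without delay; or
- state that the trial ends at the last subject's Visit 13 or discontinuation. This also covers any gap between registration and implantation.

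The cost is an administrative amendment and a trial period longer by up to about 3 to 4 months. Closing registration earlier instead is not advisable: stopping on 24 August 2025 would forgo about one subject under uniform accrual, as many as are exposed. No change to the device, storage or follow-up periods is implied.

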## 4. Subject selection, exclusion, and discontinuation criteria

Patients who give written consent to participate in the clinical trial, who meet all of the "4.2 Inclusion Criteria" at the time of registration, and who do not violate any of the "4.3 Exclusion Criteria" will be considered as subjects of this clinical trial.

### 4.1 Target diseases

Patients with severe lower limb ischemia who require bypass surgery to connect to the calf artery or foot artery below the knee, but who do not have an appropriate autologous vein.

#### 4.2 Selection Criteria

- (1) Patients who have given written consent to participate in the clinical trial
- (2) Patients who are 18 years of age or older at the time of consent
- (3) Patients with severe lower limb ischemia who meet the comprehensive WIfI classification of chronic limb threatening ischemia (CLTI) severity criteria (reference 15) of ischemia grade 2 or 3 (ABI <0.6, SPP <40 mmHg)
- (4) Patients who are recommended to undergo lower limb artery bypass surgery and who meet any of the following criteria:
  - a: Stage III limb ischemia according to the Global Anatomic Staging System (GLASS) classification of the Global Vascular Guideline (GVG) (Reference 8) and clinical stage 2, 3, or 4 according to the WIfI classification
  - b: GLASS stage II limb ischemia and clinical stage 3 or 4 of the WIfI classification
  - c: GLASS stage I or II limb ischemia in which sufficient blood flow cannot be achieved even with endovascular treatment (including clinical failure in which the wound does not heal and clinical symptoms do not improve)
- (5) Patients who do not have an appropriate upper or lower limb vein (or lower limb vein in the case of dialysis patients) that meets the length and diameter ( $\geq 3$  mm) required for bypass surgery (References 16 - 18) and has no abnormal findings such as aneurysm
- (6) Patients who require peripheral anastomosis of a bypass to a calf artery below the knee or a foot artery
- (7) Patients who are judged to be able to survive for  $\geq 12$  months and be able to be followed up for 12 weeks after bypass surgery at the time of obtaining informed consent

[Rationale for setting]

- (1), (2), (7) To select appropriate patients from ethical and safety standpoints
- (3) To select patients who require revascularization
- (4) To select patients who are best suited to bypass surgery when selecting a treatment method
- (5) To select patients who do not have a suitable autologous vein for a bypass graft
- (6) Because existing artificial blood vessels cannot be used as a bypass graft in this area

#### 4.3 Exclusion criteria

- (1) Patients whose general condition makes it difficult to secure the implantation period of the test device required for biotube formation due to reasons such as the need for immediate revascularization.
- (2) Patients whose general condition makes it difficult to tolerate surgery due to severe malnutrition (CONUT score 8-12) (Reference 19) or severe complications, etc.
- (3) Patients who may not be able to secure two or more implantation sites for the test device due to reasons such as poor skin condition or a history of exposure to subcutaneous implants in the past.
- (4) Patients who had undergone invasive surgery within 30 days prior to enrollment (excluding those undergoing treatment for leg wounds)
- (5) Patients who do not have a peripheral target artery required for bypass surgery or who have a history of endovascular treatment at the site of the proposed peripheral anastomosis
- (6) Patients who have arterial occlusion proximal to the planned central anastomosis site for bypass surgery
- (7) Patients who cannot confirm blood circulation distal to the planned peripheral anastomosis site of bypass surgery (excluding those who can confirm collateral circulation)
- (8) Patients who have had a lower limb amputation proximal to the midfoot
- (9) Patients with a history of or comorbid malignant tumors (excluding those who have had no recurrence or new onset for more than 5 years after treatment)
- (10) Patients who are using immunosuppressants due to comorbid autoimmune diseases or after transplantation, etc.
- (11) Patients with a history of allergies to stainless steel or polyolefin resins
- (12) Patients who are pregnant or may be pregnant
- (13) Patients who are participating or planning to participate in other clinical trials or interventional clinical studies
- (14) Patients who are judged by the investigator or co-investigator to be inappropriate for this clinical trial due to medical condition or safety reasons.

[Rationale for setting]

- (1), (2), (4), (9)-(12) To ensure the safety of subjects
- (3), (5)-(8) To properly evaluate the efficacy and safety of the test device
- (13), (14) To conduct the clinical trial ethically and safely

